## Abstract

**Background:**

In a pilot study using both cannabidiol (CBD) and tetrahydrocannabinol (THC) as single agents in advanced cancer patients undergoing palliative care in Thailand, the doses were generally well tolerated, and the outcome measure of total symptom distress scores showed overall symptom benefit. The current study aims to determine the intensity of the symptoms experienced by breast cancer patients, to explore the microbiome profile, cytokines, and bacterial metabolites before and after the treatment with cannabis oil or no cannabis oil, and to study the pharmacokinetics parameters and pharmacogenetics profile of the doses.

**Methods:**

A randomized, double-blinded, placebo-controlled trial will be conducted on the breast cancer cases who were diagnosed with breast cancer and currently receiving chemotherapy at King Chulalongkorn Memorial Hospital (KCMH), Bangkok, Thailand. Block randomization will be used to allocate the patients into three groups: Ganja Oil (THC 2 mg/ml; THC 0.08 mg/drop, and CBD 0.02 mg/drop), Metta Osot (THC 81 mg/ml; THC 3 mg/drop), and placebo oil. The Edmonton Symptom Assessment System (ESAS), Food Frequency Questionnaires (FFQ), microbiome profile, cytokines, and bacterial metabolites will be assessed before and after the interventions, along with pharmacokinetic and pharmacogenetic profile of the treatment during the intervention.

**Trial registration:**

TCTR20220809001.

## Introduction

Breast cancer patients reported lower quality of life (QoL) globally [1–3], and chemotherapy was a factor in worsening QoL among the patients [4]. Despite standard medical treatment, the impact of integrating complementary and alternative medicine was introduced into the current practice [5]. Therefore, cannabinoids from *Cannabis sativa* have become attractive due to their major impact in reducing pain associated with chemotherapy and tumor-associated symptoms [6–8].

### Clinical evidence of THC and CBD in cancer patients

In a pilot study using both cannabidiol (CBD) and tetrahydrocannabinol (THC) as single agents in advanced cancer patients undergoing palliative care, the doses of THC and CBD were generally well tolerated, and the outcome measure of total symptom distress scores (TSDSs) showed overall symptom benefit [9].

A first nationwide prospective observational cohort had been conducted at 22 sites in 18 provinces of 13 regions in Thailand (Thai Clinical Trial Registry No. TCTR20191231001; Ethical Approval No.36/2562). The study found that practice patterns of Thai cannabis oil could vary across institutions. One drop daily before bedtime was the most common practice and could significantly improve the QoL assessed by using both EQ-5D-5 L and Edmonton Symptom Assessment Scale (ESAS) of cancer individuals including breast cancer.

### Gut microbiota in breast cancer

The human microbiota plays a crucial role in regulating steroid hormone metabolism, primarily through enzymes like hydroxysteroid dehydrogenase [10, 11]. While there’s no conclusive evidence linking dysbiosis to breast cancer, studies comparing breast samples have shown differences in microbial abundance and diversity between healthy individuals and patients [12, 13]. Additionally, less fungal diversity and richness has been seen in cancer patients [14]. Varied hormonal subtypes of breast cancer are associated with distinct fungal signatures in the tumor microenvironment, with estrogen receptor-positive breast cancer patients displaying higher fungal diversity than those with triple-negative breast cancer [15, 16]. Gut dysbiosis can also dysregulate immune responses and their metabolic products like short chain fatty acids influence mucosal immunity [17].

### Skin microbiota in breast cancer

Although the function of breast skin microbiota remains unclear, it is associated with high abundances of skin commensals, notably various *Staphylococcus* species [18]. Potential pathways for microbial transfer to underlying tissue include retrograde transfer through ductal networks, epidermal barrier permeabilization, and migration through nipple-aspirate fluid [18].

### Oral microbiota in breast cancer

There are indications of a relationship between breast cancer and the oral microbiome, with studies suggesting that women with periodontal disease, caused by specific bacteria including the red complex (*Porphyromonas gingivalis, Tannerella forsythia*, and *Treponema denticola*) and the orange complex (*Fusobacterium nucleatum, Prevotella intermedia, Prevotella nigrescens, Peptostreptococcus micros, Streptococcus constellatus, Eubacterium nodatum, Campylobacter showae, Campylobacter gracilis*, and *Campylobacter rectus*), have an elevated risk of breast cancer [19–21].

### Cannabinoids and microbiota

Nearly all the effects of cannabinoids are mediated by cannabinoid (CB) receptors such as CB1 and CB2 receptors, which are predominantly expressed in the brain and immune cells, respectively [22–24]. The gut-brain axis and bacterial metabolites and products have recently come to light as a mechanism by which intestinal bacteria can influence the physiology and inflammation of the central nervous system [25]. These mechanisms are dysregulated and then linked to altered blood-brain barrier permeability and neuroinflammation during dysbiosis [25]. The positive effects of cannabinoids on the GI and immunological systems are lowering intestinal permeability, controlling intestinal bacteria, and reducing inflammation, according to earlier preclinical studies [26, 27].

### Clinical practice in Thailand

Currently, the Herb and Thai Traditional Medicine Development Division, Department of Thai Traditional and Alternative Medicine (DTAM), Ministry of Public Health, Thailand, manufactures Metta Osot (THC 81 mg/ml; THC 3 mg/drop) and Ganja Oil (THC 2 mg/ml; THC 0.08 mg/drop and CBD 0.02 mg/drop), both of which are produced under license number 13/2562 and has been added to the National List of Essential Medicines [28]. The preliminary analysis of the Thai Cannabis Practice Patterns and QoL (Thai Cannabis PQ) study assessed the pain symptoms using the ESAS and QoL using the EuroQoL Group’s 5-dimension, 5-level (EQ-5D-5 L). It revealed that QoL and all ESAS symptoms improved significantly at 1 month (*p* < 0.001), of which feeling of wellbeing (1.00 ± 2.34), pain (0.95 ± 2.39), tiredness (0.93 ± 2.51), and anxiety (0.85 ± 2.25) showed the largest mean differences [29].

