## Materials and methods

### Target population

We include 90 adult breast cancer women patients who were diagnosed with breast cancer or currently receiving chemotherapy at King Chulalongkorn Memorial Hospital (KCMH) with an anticipated starting recruitment approximately in August 2023. The sample size was calculated using the mean ESAS values of the previous study [29].

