#### Trial timepoints

Assessment of adverse drug effects will be collected with 4 time points: 0th, 1st, 6th, 12nd weeks of the trial day. The pain symptoms, QoL and diet pattern will be recorded with 3 time points: 0th, 6th, 12nd weeks. The blood collection (3 mL) for pharmacokinetic and pharmacogenetic tests will be performed on 2 time points: 0th, 6th weeks. The blood (10 mL), feces, skin scrapping, and saliva samples will be taken for biochemistry tests (plasma/ serum), microbiome (gut/ skin/ saliva), cytokines (plasma) and bacterial metabolites (serum/ feces) will be analyzed at 2 time points: 0th, 12nd weeks. The overview of the tests and visits of the clinical trial was shown on the following Table 1.

**Table 1 Tab1:** SPIRIT schedule of enrolment and assessments

#	Timepoint	Week-0 baseline	Week-1 follow-up	Week-6 follow-up	Week-12 follow-up
		T1	T2	T3	T4
1	**Enrolment**				
	Eligibility screening	x			
	Informed consent	x			
	Allocation	x			
2	**Assessment**				
	CRF01 Case Record Form^a^	x			
	CRF02 FW & ADR^b^	x	x	x	x
	CRF03 ESAS	x		x	x
	CRF04 EQ-5D-5 L	x		x	x
	CRF05 Food Frequency Questionnaire	x		x	x
3	**Blood Samples, Serum**				
	Blood Chemistry^c^	x			x
	Cytokines^d^	x			x
	Bacterial Metabolites^e^	x			x
	Pharmacokinetics parameters	x		x	
	Pharmacogenetics parameters	x		x	
4	**Feces Samples**				
	Fecal Microbiome Profile	x			x
	Fecal Bile Acid Profile^f^	x			x
	Fecal SCFAs^g^ and BCFAs^h^	x			x
5	**Skin Samples**				
	Skin Microbiome Profile	x			x
6	**Saliva Samples**				
	Oral Microbiome Profile	x			x

^a^Demographic and Epidemiological Factors: age, weight, height, waist circumference, hip circumference, neck circumference, alcohol consumption, smoking status, occupation, monthly income, method of health payment, and highest education

^b^Follow up and adverse drug reaction: vital signs, physical examination, lab results to assess liver, kidney and heart function, pharmacokinetic record form, drug tolerance assessment form, and adverse event assessment form

^c^Blood Chemistry: lipid profile, liver function test (LFT)

^d^Cytokines: interleukin-17, interferon-gamma, Interleukin-10, tumor growth factor-beta

^e^Bacterial Metabolites: lipopolysaccharide binding protein, sCD14 levels, equol, cadaverine

^f^Fecal Bile Acid Profile: chenodeoxycholic acid, deoxycholic acid, lithocholic acid

^g^SCFAs: butyric acid, propionic acid, acetic acid

^h^BCFAs: iso-butyric acid

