### Primary outcome measures

The pain level of each patient will be assessed using the ESAS form at the last visit as primary outcome.

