### Secondary outcome measures

#### Pain level assessment

The ESAS at 0^th^, 6^th^ weeks visits will be taken as secondary outcome measures and will be evaluated all the symptoms.

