### Statistical considerations

#### Sample size estimation

We target 30 patients in each arm, considering the maximum follow-up loss of 50%. Since the target population is metastatic breast cancer cases, questionnaires and biological samples such as blood, stool, saliva, and breast skin scrapping will be collected before and after the treatment, which could increase the withdrawal rate at any time during the trial.

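### ESAS is not taken at the existing week-1 visit, so women who leave before week 6 give no on-treatment pain score; adding it is a cheap improvement

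*Protocol article*

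**What the plan says.** The protocol article is consistent on when pain is measured. Under Trial timepoints: "The pain symptoms, QoL and diet pattern will be recorded with 3 time points: 0th, 6th, 12nd weeks". Table 1 agrees: the ESAS form (CRF03) is marked at T1, T3 and T4 and left blank at T2, the week-1 visit. That visit exists for safety: "Assessment of adverse drug effects will be collected with 4 time points: 0th, 1st, 6th, 12nd weeks of the trial day". At week 1 only the follow-up and adverse-reaction form (CRF02) is completed.

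The primary outcome is fixed at week 12: "The pain level of each patient will be assessed using the ESAS form at the last visit as primary outcome". Earlier scores are secondary: "The ESAS at 0^th^, 6^th^ weeks visits will be taken as secondary outcome measures". Sample size estimation sets 30 women per arm, "considering the maximum follow-up loss of 50" per cent, and expects that withdrawals may come at any point. Statistical analysis promises intention to treat and names one-way ANOVA or Kruskal-Wallis for comparing the three arms.

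The only quantified ESAS effect is in Clinical practice in Thailand, from the study that also informed the sample size: "It revealed that QoL and all ESAS symptoms improved significantly at 1 month", with "pain (0.95 ± 2.39), tiredness (0.93 ± 2.51), and anxiety (0.85 ± 2.25) showed the largest mean differences".

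**The concern.** With up to half the women expected to be lost, missing week-12 pain scores are a main threat to the intention-to-treat result. What can be done about them depends on what was recorded before each woman left. A woman lost between weeks 6 and 12 leaves one on-treatment score. A woman lost before week 6 leaves only her baseline.

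If some women leave early because their pain is not improving, and this differs between arms, nothing recorded about their pain separates them from those who stay. A mixed model or imputation built on weeks 0, 6 and 12 cannot then correct the comparison. An analysis plan that is not shown could choose a better method, but it could not supply a score that was never collected. The schedule therefore has to be settled in the protocol.

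**Working it through.** **1. How many women are affected**

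Inputs: 90 women, 30 per arm, and a maximum loss of 50% by week 12 (Target population; Sample size estimation). At that maximum, 90 × 0.5 = 45 women are lost. The article does not say when, so two patterns are assumed.

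| Pattern | Formula | Lost before week 1 | Lost before week 6 |
|---|---|---|---|
| Linear | 0.5 × t/12 | 4.2%, 3.75 of 90 | 25%, 22.5 of 90 |
| Constant rate | 1 − 0.5^(t/12) | 5.6%, 5.1 of 90 | 29.3%, 26.4 of 90 |

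About 23 to 26 women would have no on-treatment ESAS under the present schedule, against about 4 to 5 if ESAS were taken at week 1. The difference, 22.5 − 3.75 = 18.75 to 26.4 − 5.1 = 21.3, is about 19 to 21 women who would gain a score.

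Without assuming a pattern: if 25%, 50% or 75% of the 45 losses fall before week 6, then 11, 22 to 23, or 34 women are affected.

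**2. What a week-1 score would buy**

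This was simulated for one active arm against placebo, with a true pain difference of −0.95 and about half the women lost. The 0.95 is the cohort's before-after change. It had no control arm and is only a stand-in for a between-arm effect. All other inputs are assumptions:

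- baseline SD 1.7
- person-level response SD 1.5, 1.2 or 2.0
- residual SD 1.2, 1.4 or 1.0
- logistic slope for leaving 1.5, 1.0 or 1.5

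The model is maximum likelihood for repeated scores. Mean estimates were:

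| Why women leave | Weeks 0, 6, 12 | Weeks 0, 1, 6, 12 |
|---|---|---|
| A. Placebo: poor early change; active: at random; full response by week 1 (three spreads) | −0.45, −0.69, −0.25 | −0.96, −0.97, −0.92 |
| B. As A, half or a quarter of the response present at week 1 | −0.43 to −0.83 | −0.93 to −1.02 |
| C. As A, but leaving follows an unrecorded state at about week 3 | −0.34 to −0.72 | −0.55 to −0.84 |
| D. As A (first spread), leaving follows change at the time of leaving, after week 1 | 0.01 | −0.37 |
| E. As D, a quarter of the response present at week 1 | −0.06 | −0.21 |
| F. Poor response in both arms, full response by week 1 | −0.81 | −0.94 |
| G. As F, a quarter of the response present at week 1 | −0.97 | −0.98 |
| H. Leaving follows pain level | −0.93 | −1.01 |

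Row A used 200 trials of 30 per arm; D to G used 300 trials of 30 per arm; B and C used 20,000 per arm to isolate bias. A repeat of A at 20,000 per arm gave −0.55, −0.70 and −0.37 without week 1, and −0.97, −0.96 and −0.96 with it. Completers alone, in the settings of A, gave −0.26, −0.71 and +0.15.

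With about 15 completers per arm and SD 2.39, the Monte Carlo error over 200 trials is about 2.39 × √(2/15) / √200 = 0.06. Differences of a few hundredths should not be read.

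**3. Reading the table**

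- When leaving follows the recorded early response in one arm only (A, B), the week-1 score removes nearly all the bias.
- When leaving follows a later, unrecorded state (C, D, E), it removes part. In D the error falls from 0.96 to 0.58.
- When both arms leave for the same reason (F, G), or leaving follows pain level (H), the gain is small or nil: 0.13 in F, and none in G and H.

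**The case against.** The strongest reply is that this is a consistent schedule and an extra assessment is a preference. Several parts of that reply stand.

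- **No contradiction.** The text, Table 1 and the outcome sections agree with one another.
- **The 1-month result.** A reader might infer that the trial misses the time at which the earlier effect was seen and that a week-1 score would restore it. It would not. One month is about week 4.3, so week 6 is 1.7 weeks away and week 1 is 3.3 weeks away.
- **Direction.** A reader might infer that the bias must run towards no effect. It does in rows A to E because women on placebo were made to leave on poor response and women on oil at random. The article links withdrawal to metastatic disease and to the burden of questionnaires and samples. It also lists side effects such as sedation and decreased appetite, which could drive leaving on active oil.
- **Near-complete recovery.** Row A makes leaving depend on the very score being added, so recovery is built in. Rows C to H show how far it weakens.
- **Nothing recorded about leavers.** This would go too far. CRF02 at week 1 includes drug-tolerance and adverse-event forms, so that reason for leaving is captured. Early pain response is not.
- **Analysis.** ANOVA or Kruskal-Wallis on week-12 scores makes no use of interim scores. The handling of missing data may be in an analysis plan that is not shown.

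What remains is that early pain response goes unrecorded at a visit already planned, in a trial that expects heavy loss. In the mechanisms tried, the extra score either moved the estimate towards the truth or made little difference.

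**Conclusion.** The point holds as a cheap improvement, not as an error in the plan. Women who leave before week 6 will have no on-treatment pain score. That is about 23 to 26 of 90 if loss reaches the 50% maximum and is linear or at a constant rate, and fewer if loss is lower or later. If leaving depends on early pain response, the week-12 comparison can be biased. The documents fix neither the size nor the direction. A week-1 score would help anywhere from hardly at all to substantially, most when early response drives leaving in one arm only. These results rest on assumed dropout timing, assumed response spreads and a two-arm simplification. They show a range of possible gain, not a forecast for this trial.

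**What to change.** Mark CRF03 (ESAS) at T2 in Table 1, and change Trial timepoints so that pain is recorded at weeks 0, 1, 6 and 12. List the week-1 score with the other secondary ESAS times under Pain level assessment.

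The score helps only if it is used. For the primary week-12 comparison, specify a mixed model for repeated measures or multiple imputation that includes the week-1 and week-6 scores, in place of an ANOVA or Kruskal-Wallis test confined to women with a week-12 score. The week-1 tolerability data on CRF02 could be added to an imputation model as auxiliary information.

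Cost: one mark in the table, matching edits to two sections, and a few minutes more per woman at a visit she already attends. It adds slightly to the questionnaire burden that the article itself links to withdrawal. No visit, sample or treatment changes. It must be done before women pass week 1, because the score cannot be recovered afterwards.

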### Pharmacokinetic and pharmacogenetic profile

The pharmacokinetic profile of cannabinoids depends on routes of medication such as oral dosage and inhalation. A study revealed that the median value of the time taken to achieve the highest levels (T_max_) of sublingual drops for CBD only and a combination of CBD and THC was 2.17 h (range 1–4 h) and 1.67 h (range 1–3 h) and the highest concentration of the drops (C_max_) was 2.05 ± 0.92 and 2.58 ± 0.68 nanograms/ml, respectively [30]. In contrast, our understanding of the therapeutic potential of cannabinoids remains limited. To enhance our knowledge regarding the proteins and molecules responsible for the transport, action, and metabolism of cannabinoids in humans, we will evaluate specific candidate genes identified in previous reviews [31].

### Adverse events and the safety measures

It is crucial to thoroughly describe the evidence of health effects and hazards in conjunction with the legalization of cannabis use. A summary review of marijuana use revealed that the link between testicular cancer and the drug has the highest quality score, followed by the links to psychosis, suicide deaths, functional and structural integrity, memory and learning, anhedonia, the amygdala, attention, memory, overall activity, and other things [29]. A systematic review of CBD’s side effects found that pneumonia (OR 5.37, 95% CI: 1.17–24.65), decreased appetite (OR 3.56, 95% CI: 1.94–6.53), diarrhea (OR 2.61, 95% CI: 1.46–4.67), somnolence (OR 2.23, 95% CI: 1.07–4.64), and sedation (OR 4.21, 95% CI: 1.18–15.01) were all associated with a higher risk of experiencing [30]. In the current study, the side effects of the cannabis oil have been monitored in the previous clinical practice [29]. The patients suspected of having the cannabis allergy will be excluded during the recruitment, and the adverse events will be assessed using the case record form in every follow up visits.

### Summary of the study

Hence, the current randomized study aims to explore the efficacy of Thai cannabis oil products on the QoL of individuals diagnosed with breast cancer and treated with chemotherapies, along with the study of microbial alteration and diversity by cannabis and pharmacokinetic measures among those patients. We aim to determine the intensity of the pain and QoL experienced by cancer patients using the ESAS and the EQ-5D-5 L forms, respectively, to explore the microbiome profile, cytokines, and bacterial metabolites in hormone-dependent and independent breast cancer patients before and after the treatment with the cannabis oil or no cannabis, and to study the pharmacokinetics parameters and pharmacogenetics profile.

## Materials and methods

### Target population

We include 90 adult breast cancer women patients who were diagnosed with breast cancer or currently receiving chemotherapy at King Chulalongkorn Memorial Hospital (KCMH) with an anticipated starting recruitment approximately in August 2023. The sample size was calculated using the mean ESAS values of the previous study [29].

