#### Patient allocation and blinding

The recruited patients will be randomly allocated into 3 groups: Ganja Oil (THC 1.701 mg/mL or 0.068 mg/drop; CBD 0.003 mg/mL or 0.0001 mg/drop; CBN 0.170 mg/mL or 0.007 mg/drop; COA Ganja Oil TRCM65/05232), Metta Osot (THC 77.622 mg/mL or 3.105 mg/drop; CBD 6.737 mg/mL or 0.2695 mg/drop; CBN 7.406 mg/mL or 0.296 mg/drop; COA Metta Osot TRCM64/33,743 Rev.1), and placebo oil (THC 0 mg/mL or 0 mg/drop; CBD 0 mg/mL or 0 mg/drop; CBN 0 mg/mL or 0 mg/drop; COA Placebo TRCM64/33,742) groups. The allocation will be conducted with a 1:1:1 ratio using block randomization with a block of six by the table of random numbers for creating randomization ID. The research team will provide the randomization code in an opaque envelope to conceal allocation, mask clinicians, data collectors, and patients. Following the cannabis practice patterns of the preliminary study [29], all the participants will be received cannabis or placebo oil once per day before bedtime for 12 weeks.

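### The ESAS changes printed from the earlier study do not support 30 randomised per arm for a between-arm comparison of pain at week 12

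*Protocol article*

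**What the plan says.** - **Basis of the size** (Target population): "The sample size was calculated using the mean ESAS values of the previous study [29]". The same section gives the total: "We include 90 adult breast cancer women patients".
- **Size and loss** (Sample size estimation): "We target 30 patients in each arm, considering the maximum follow-up loss of 50" per cent. No target difference, SD, test or power is given there.
- **Reason for the loss allowance** (same section): "Since the target population is metastatic breast cancer cases, questionnaires and biological samples" will be collected before and after treatment, which is expected to raise withdrawal.
- **Population** (Inclusion criteria): women with breast cancer of any stage who are on chemotherapy or about to start it.
- **Primary outcome** (Primary outcome measures): "The pain level of each patient will be assessed using the ESAS form at the last visit as primary outcome". The last visit is week 12.
- **Design** (Patient allocation and blinding): "The allocation will be conducted with a 1:1:1 ratio using block randomization".
- **Earlier results** (Clinical practice in Thailand): "all ESAS symptoms improved significantly at 1 month". The section lists the four largest mean differences. Pain is given as "pain (0.95 ± 2.39"), with wellbeing 1.00 ± 2.34, tiredness 0.93 ± 2.51 and anxiety 0.85 ± 2.25.
- **Analysis** (Statistical analysis): one-way ANOVA with Bonferroni correction across the three arms, or Kruskal-Wallis for non-normal data. Significance is p < 0.05. The section also says that multiple analyses were not corrected for.

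**The concern.** The article names a source for its sample size and prints figures from that source, but the figures and the size do not connect. The printed pain change calls for several times the planned number. It is also a before-after change in an uncontrolled cohort at one month, whereas this trial compares oil with placebo at 12 weeks. Part of an uncontrolled change can occur on placebo too, so taking all of it as the difference between arms is generous to the plan.

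A reader who accepts the sentence will assume that the trial can detect an effect of the size seen before. If it cannot, a non-significant result would say little about whether the oils relieve pain, and nothing in the article warns of this. The loss allowance matters as well: it can halve the evaluable sample, and the reason given for it describes a narrower population than the one to be enrolled.

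**Working it through.** **Inputs from the article.** 30 randomised per arm; maximum loss 50%; three arms, 1:1:1; alpha 0.05; pain change 0.95 with SD 2.39.

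**Assumptions.** Two-sided tests; 80% power; Bonferroni for three pairwise comparisons, 0.05/3 = 0.0167. Both alpha levels are shown because the article mentions Bonferroni and also says that multiple analyses are not corrected. To begin with, the SD of the week-12 pain level is set equal to 2.39.

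**1. The plan's own figure.** 30 × (1 − 0.50) = 15 evaluable per arm, and 15/(1 − 0.50) = 30. The loss step is consistent. What remains is where the 15 comes from.

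**2. Number needed for the printed pain change.** d = 0.95/2.39 = 0.397.
- Between two arms, normal approximation: n = 2(1.960 + 0.842)²/d² = 99.4 per arm. The t-test gives 100.3, so 101. At alpha 0.0167 the t-test gives 134.
- Before-after within one arm: n = (1.960 + 0.842)²/d² = 49.7. The paired t-test gives 51.6, so 52.
- Three-arm ANOVA with two arms equal and the third 0.95 away: about 277 in total, or 92 to 93 per arm.

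**3. The other printed items** (t-test, two-sided 0.05, 80% power):

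| Item | d | Per arm, between arms | Pairs, within one arm |
|---|---|---|---|
| Wellbeing | 0.427 | 87 | 45 |
| Pain | 0.397 | 101 | 52 |
| Anxiety | 0.378 | 111 | 57 |
| Tiredness | 0.371 | 116 | 60 |

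The most lenient single-item reading, wellbeing with a one-sided paired test, still needs 36.

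**4. Power and precision at the planned size** (pain, difference 0.95, SD 2.39). The half-width is t × 2.39 × √(2/n) on 2n − 2 degrees of freedom.

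| Evaluable per arm | Power, 0.05 | Power, 0.0167 | Detectable at 80%, 0.05 | Detectable at 80%, 0.0167 | 95% CI half-width |
|---|---|---|---|---|---|
| 15 | 18% | 9% | 2.5 | 3.0 | 1.8 |
| 30 (no loss) | 33% | 19% | 1.8 | 2.0 | 1.2 |

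A paired test within one arm with all 30 retained has 56% power.

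**5. Sensitivity to the SD.** 2.39 is the SD of a change, but the outcome is a level. With equal variances at both times and correlation r, SD(level) = 2.39/√(2(1 − r)). Alpha is 0.05, unadjusted.

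| Assumed r | SD of level | Power, 15 | Power, 30 | Detectable, 15 | Detectable, 30 | Needed per arm |
|---|---|---|---|---|---|---|
| 0 | 1.69 | 32% | 57% | 1.8 | 1.2 | 51 |
| 0.5 | 2.39 | 18% | 33% | 2.5 | 1.8 | 101 |
| 0.8 | 3.78 | 10% | 16% | 4.0 | 2.8 | 250 |

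Nowhere in this range does power for 0.95 reach 80%.

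**6. The loss allowance.** Sample size estimation describes the target population as metastatic. Inclusion criteria set no limit on stage. Both cannot describe the enrolled patients.

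**The case against.** The strongest reply is that the article refers only to mean ESAS values of the earlier study. It does not say that the one-month changes, or pain in particular, were used. The article prints selected results of a preliminary analysis; baseline levels, total scores or a breast-cancer subset may exist and may have entered a calculation in the full protocol. This stands. A reader might infer that no calculation was made, or that the size was really set by feasibility. The documents support neither: no passage gives a feasibility basis, and the unseen values cannot be ruled out.

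Nor was every reading excluded. Summing the four printed items gives a mean change of 3.73. A paired test on that sum needs about 15 if the items are uncorrelated and about 26 (26.1) at an assumed inter-item correlation of 0.3. Zero correlation among symptoms in the same patient is hard to believe, and a within-arm test of a summed score is not the primary outcome. It therefore does not rescue the size for pain between arms, but it does rule out saying that no ESAS reading can give 15.

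The 15 is itself inferred, since 50% is called a maximum loss; hence the results for both 15 and 30. The power figures also depend on an assumed SD, so they should be quoted with their range. Finally, an article may leave the worked calculation to the full protocol, so the missing formula is not the complaint. The complaint is that the figures the article does print do not support the size it says came from that study.

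**Conclusion.** The point holds in this form: the printed ESAS changes do not support the stated size for the stated primary outcome. Between arms, the pain change needs about 101 evaluable per arm, against 15 at maximum loss and 30 at none. That is 101/15 = 6.7 or 101/30 = 3.4 times the planned number. Power for 0.95 points is 18% to 33% unadjusted and 9% to 19% with Bonferroni at SD 2.39. Allowing for the unknown SD of the level, unadjusted power runs from 10% to 57%. These results assume two-sided tests and take the full uncontrolled change as the effect against placebo.

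Two stronger readings should be avoided. The article does not claim adequate power, so it cannot be charged with a false power statement. Nor does it say how a null result will be read; the risk of misreading is a reason to add a sentence, not an error already made.

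The conflict over disease stage is real, but it is a separate matter of consistency and does not enter the power calculation.

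**What to change.** 1. In Target population, either give the ESAS values, SD, test, alpha and power that yield the size, or withdraw the sentence. Do not substitute another rationale, such as feasibility, unless the authors confirm it.
2. In either case, state under Sample size estimation what the trial can detect, with the SD assumption. For example: *Assuming an SD of 2.39 for ESAS pain at week 12, the trial has 80% power for a between-arm difference of about 1.8 points (30 evaluable per arm) to 2.5 points (15 per arm), or 2.0 to 3.0 points with Bonferroni correction. The 95% confidence interval half-width is 1.2 to 1.8 points. The SD is taken from a one-month change; for baseline-to-follow-up correlations of 0 to 0.8 the unadjusted detectable difference is about 1.2 to 4.0 points.*
3. Add that a non-significant primary result will be interpreted through its confidence interval.
4. Reconcile the metastatic population in Sample size estimation with the any-stage inclusion criterion, and base the 50% loss allowance on the patients actually enrolled.

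The cost is wording only. No patients are added, though the stated detectable difference will look less favourable than the present sentence implies.
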